### Data analyses

Intention-to -treat analyses and per protocol analyses will be performed, and CONSORT recommendations will be followed [98]. First, the three groups will be compared to verify that there are no significant differences among them at baseline on the outcome measures in order to confirm that they are comparable after randomization. One-way ANOVAs for continuous variables and Chi-squared tests of independence for categorical ones will be used. For the continuous outcome measures on the posttest, the homoscedasticity assumption will be assessed with the Levene test. Where this assumption is met, the usual *F*-test will be applied to compare the posttest means for the three experimental conditions. If the homoscedasticity assumption is not met, the Brown-Forsythe *F*-test will be applied. Statistically significant *F*-tests will be followed by post hoc comparisons. In particular, the Tukey procedure will be applied where the homoscedasticity assumption is met, and the Games-Howell procedure if this assumption is not met.

The intention-to-treat principle will be used when analyzing primary and secondary post-treatment data and data collected at the 3- and 12-month follow-ups, using mixed-effect models with full information maximum likelihood estimation. This method has been recommended due to its flexibility on repeated-measures ANOVAs in handling missing data more appropriately [99]. To complement the results of the ANOVAs and post hoc comparisons, effect sizes will be calculated by using the standardized mean difference proposed by Cohen [62]. These effect sizes will be calculated to assess both within- and between-group changes, all of them based on a pooled standard deviation.

Although per protocol analyses (completers only analysis) suffer from selection bias, they will also be conducted to help to draw conclusions about the maximum treatment efficacy in patients who comply fully with the treatment [100].

When the trial ends, the analytic methodology for the RCT will be reviewed before analyzing the data in order to select the most appropriate analytic procedures.

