## Methods/Design

### Study design

A three-armed randomized controlled trial (RCT) will be conducted. Participants will be randomly allocated to one of three conditions: a) *Transdiagnostic Internet-based protocol (TIBP)*, b) *Transdiagnostic Internet-based Protocol + Positive Affect component (TIBP + PA),* and c) *Waiting List control condition (WL)*. For ethical reasons, participants in the control condition will be offered the possibility of receiving the treatment protocol. Block randomization will be performed within each stratum in order to ensure that all primary diagnoses are equally represented across conditions. Measures will be taken at post-randomization, after the treatment, and at 3- and 12-month follow-ups, in order to test whether the improvements achieved during the therapy are maintained in the long term.The study flowchart is shown in Fig. 1. The study will be conducted following the CONSORT statement (Consolidated Standards of Reporting Trials, http://www.consort-statement.org) [57, 58] the CONSORT-EHEALTH guidelines [59], and the SPIRIT guidelines (Standard Protocol Items: Recommendations for Interventional Trials) [60, 61].

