### Sample size

To determine the sample size, the effect sizes found in the literature have been considered. An RCT using the UP in a traditional face-to-face approach [33] obtained effect sizes of 0.56 for anxiety, measured with the BAI, and 1.11 for depression, measured with BDI-II. The mean effect size indicated in a recent meta-analysis [39] comparing transdiagnostic computerized cognitive-behavior therapy (CBT) to waitlist control was g = .93 for anxiety and g = .88 for depression.

Adopting a more conservative approach than those of the aforementioned studies, we assumed an effect size of 0.5 (Hedges’ g), which, following Cohen [62], can be considered an effect size of medium magnitude. As our design included three experimental conditions (*TIBP*, *TIBP + PA*, *WL*), a between-groups one-way ANOVA was assumed for the statistical analyses. Therefore, calculations of the necessary sample size cannot be based on Hedges’ *g* index for effect size, but rather on the *f* index [62]. Following Cohen [62], *f* = 0.25 represents an effect size of medium magnitude (and equivalent to *g* = 0.5). Thus, considering an alpha of .05 and a statistical power of .80, the total sample size required to warrant these conditions contains 159 participants (53 participants per group). To control the maximum possible loss of subjects during treatment, based on the literature about Internet-based treatments, a 30% dropout rate is expected [53, 63]. Thus, the required sample size should have 207 participants in all (69 participants per group). These calculations were accomplished with the software program *G*Power 3.1* [64].

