### Ethics

The study follows the guidelines of the Declaration Helsinki and existing guidelines in Spain and the European Union for the protection of patients in clinical trials. As noted, all participants will be volunteers, and they will sign the online informed consent to form part of the study once it has been explained to them. Participants will have the possibility of withdrawing from the study at any time. The recruitment of participants will be carried out by qualified personnel from a clinical point of view. Participants allocated to the *WL* condition will be offered the opportunity to receive the *TIBP* or the *TIBP + PA* intervention after the waiting time has ended. Based on the literature, no special difficulties are expected. However, any undesired event would not only mean the participant’s departure from the trial, but s/he would also be offered the possibility of receiving psychological care at the Emotional Disorder Clinic in Universitat Jaume I, or of being referred if his/her medical condition required it.

A fundamental aspect in a project of this nature is data protection. To protect information, strategies using personal passwords and data via AES encryption (AES-256; Advanced Encryption Standard) will be used. Personal data will be replaced by codes and data, which must be collected by clinicians (e.g. age, sex, address, and phone), stored separately from other data, and only made available to researchers responsible for the study, always protecting the right to privacy.

The study has been approved by the Ethics Committee of Universitat Jaume I (Castellón, Spain). The trial was registered at clinicalstrial.gov as NCT02578758.

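### Two analyses are prescribed for the same post-treatment outcomes, an unadjusted post-test ANOVA and an intention-to-treat mixed model, and neither is named as decisive

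*Protocol article*

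**What the plan says.** All of this is in the protocol article.

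- **Data analyses, first paragraph.** The three arms are first tested for significant differences at baseline. After a Levene check, the usual F-test "will be applied to compare the posttest means for the three experimental conditions"; the Brown-Forsythe version replaces it if variances differ. Significant results are followed by Tukey or Games-Howell comparisons. No covariate, stratum term or imputation is mentioned.
- **Data analyses, second paragraph.** "The intention-to-treat principle will be used when analyzing primary and secondary post-treatment data" and the follow-up data, "using mixed-effect models with full information maximum likelihood estimation". The stated reason is better handling of missing data. Effect sizes are then calculated "To complement the results of the ANOVAs and post hoc comparisons".
- **Data analyses, last sentence.** The methodology is to be reviewed once the trial ends, before the data are analysed, "in order to select the most appropriate analytic procedures".
- **Sample size.** "a between-groups one-way ANOVA was assumed for the statistical analyses", with 159 evaluable participants, 30% expected dropout and 207 randomised.
- **Study design.** "Block randomization will be performed within each stratum in order to ensure that all primary diagnoses are equally represented across conditions".
- **Ethics.** Waiting-list participants "will be offered the opportunity to receive the" active protocols once their waiting time is over.

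**The concern.** Two analyses answer one question on different sets of participants. A one-way ANOVA with no imputation uses only those with an observed post-test. A likelihood-based mixed model can use all randomised participants who contribute data. The two can disagree, and the plan does not say which would then stand.

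The ANOVA is the test the trial is sized on, and the arm contrasts and effect sizes hang on it. It is also the less precise of the two and the more exposed to unequal dropout. It makes no use of the baseline score or of the factor used to stratify randomisation. The baseline significance tests do not make up for this, because under sound randomisation they are uninformative and they correct no imbalance.

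**Working it through.** **Inputs from the Sample size section:** three arms, f = 0.25, alpha 0.05, power 0.80, 159 evaluable, 30% dropout, 207 randomised. **Not in the document, so assumed:** the correlation r between baseline and post-test score, and the dropout mechanism in step 4.

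**1. Reproduce the plan's figure.** For a one-way ANOVA with noncentrality N × f² and 2 and N − 3 degrees of freedom, the smallest N reaching 0.80 is 158, or 159 in equal arms. At 159 the noncentrality is 159 × 0.0625 = 9.94 and power is 0.805. The figure of 159 reproduces.

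**2. Number of post-tests if 30% are lost.** 207 × 0.70 = 144.9, about 145. The noncentrality is then 9.06 and power is 0.764. This fall from 0.805 comes from the dropout allowance (159 × 1.30 = 206.7, whereas 159 / 0.70 gives 228 in equal arms). It is not caused by leaving out covariates, so both starting points are shown below.

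**3. Add baseline as one covariate.** The effect size becomes f / √(1 − r²), and one residual degree of freedom is lost.

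| r (assumed) | adjusted f | power at 159 | power at 145 | evaluable N for 0.80 |
|---|---|---|---|---|
| none | 0.250 | 0.805 | 0.764 | 159 |
| 0.3 | 0.262 | 0.843 | 0.805 | 144 |
| 0.5 | 0.289 | 0.908 | 0.878 | 120 |
| 0.6 | 0.313 | 0.947 | 0.925 | 102 |

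At r = 0.5, adjustment removes 0.5² = 25% of the residual variance. The table describes a baseline-adjusted analysis of observed post-tests, which is a stand-in for the mixed model and not the model itself. A stratum term would add to the gain only as far as diagnosis predicts outcome, and the document gives no figure for that.

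**4. Could the two analyses part company?** This was simulated with 4,000 trials per scenario and 69 per arm, comparing the ANOVA on observed post-tests with a baseline-adjusted analysis of the same data.

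- *Real effect of 0.53 SD in both active arms (f = 0.53 × √2 / 3 = 0.25), 30% random dropout.* The two disagree on significance in 8%, 14% and 22% of trials at r = 0.3, 0.5 and 0.7.
- *No true effect; dropout in the active arms rising with baseline severity (about 37%), and 15% at random on the waiting list.* The ANOVA rejects in 6%, 10% and 15% of trials, with bias of −0.08, −0.13 and −0.18 SD. The adjusted analysis stays near 5% with no material bias.

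The second scenario illustrates one assumed mechanism and does not forecast what will happen in this trial.

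**The case against.** The strongest reply is that the plan already leans towards the mixed model. The Methods part of the Abstract puts intention-to-treat first and per-protocol second. Data analyses says completer analyses suffer from selection bias and gives missing data as the reason for the mixed model. On that reading only a label is missing. The terms of the model may also sit in a fuller protocol or analysis plan that is not shown, and the closing review is to take place before analysis.

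Part of this stands, and it rules out several stronger readings that a reader might infer:

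- *That the ANOVA is the main test.* The text never says so. The sample size, the contrasts and the effect sizes point that way, while the intention-to-treat statements point the other way.
- *That the plan ignores dropouts.* This is true of the ANOVA as described, but not of the plan as a whole.
- *That baseline is used only in the comparability test.* Within-group effect sizes need it too, and the mixed model may include it as a time point.
- *That the mixed model omits diagnosis.* Its terms are not given, so its silence on this is not a fault.
- *That waiting-list participants will serve as untreated controls at 3 and 12 months.* No such contrast is stated. The hypotheses frame follow-up as maintenance of treatment gains.

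What the reply does not remove is that the article itself prescribes both tests for the same outcomes, ties sizing and contrasts to one and the intention-to-treat principle to the other, and ranks neither. The closing review gives no criterion for choosing and no statement that it will be blind to arm.

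**Conclusion.** The point holds as an unresolved duplication of the post-treatment analysis and should be corrected. That two unranked analyses exist is plain from the text. That the ANOVA would use only observed post-tests is an inference from the absence of any imputation.

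The precision at stake depends on r. Over 0.3 to 0.6, baseline adjustment adds about 0.04 to 0.14 to power at 159 evaluable (0.843 − 0.805 to 0.947 − 0.805), and about 0.04 to 0.16 at 145 (0.805 − 0.764 to 0.925 − 0.764). A reader might put the shortfall to 0.76 down to the missing covariates. It belongs to the dropout allowance, and the unadjusted ANOVA does reach its stated power at 159. The size of any dropout bias rests wholly on the assumed mechanism.

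**What to change.** 1. Name the intention-to-treat mixed model (all randomised, full information maximum likelihood) as the primary analysis for each primary outcome. Include arm, time, arm × time, baseline score and primary-diagnosis stratum, with rare diagnoses merged. Enter baseline either as a covariate with post-baseline outcomes only or as a repeated outcome, not both. Report arm contrasts at post-treatment with 95% confidence intervals.
2. Make the post-test ANOVA with its post hoc comparisons a sensitivity analysis.
3. Replace the baseline significance tests with descriptive statistics by arm.
4. Fix this choice before anyone sees outcome data by arm, and limit the end-of-trial review accordingly.
5. For the PANAS, first reconcile Table 2, which lists no baseline assessment, with the Adaptation to the web section, which describes initial questionnaires as the pre-treatment assessment. Baseline adjustment needs that measurement.
6. If any waiting-list contrast at 3 or 12 months is intended, state that waiting-list data collected after the offer of treatment will not be treated as untreated control data.

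The cost is revised analysis wording and a few degrees of freedom. For the BDI-II and BAI, Table 2 already schedules the baseline score. For the PANAS, the cost depends on the outcome of item 5.

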## Discussion

This study describes a new Internet-based transdiagnostic treatment protocol for patients diagnosed with ED. One of the core aims of this study is to provide data from an RCT to evaluate the efficacy of this protocol in a community sample, compared to a waiting list group. This protocol includes the transdiagnostic cognitive-behavioral principles [17] designed for a wide range of anxiety and depressive disorders to down-regulate NA, and it also incorporates a specific treatment component to address PA. These two ways of delivering the protocol will be tested in order to explore the effect of adding a specific therapeutic component to up-regulate PA.

Moreover, the aim of the present study is to make progress in resolving some of the challenges in the field of mental health [101], specifically in understanding the necessary treatment components to modify clinical symptoms (depression and anxiety) and strengthen people’s resilience, making them less vulnerable [101, 102].The potential impact on basic personality dimensions (N/NA/BI) and (E/PA/BA) will also be studied. As Barlow suggests [102], personality dimensions may be malleable over time, and so it can be relevant to study the “malleability” of neuroticism. Likewise, the study will also examine whether it is possible to develop strategies to modify PA (extraversion). There is growing support in the literature for the claim that positive emotions promote flexible and creative thinking and play a fundamental role in the construction of psychological strengths and intellectual and social resources that can be useful in difficult situations in the future [103–106]. Some studies have proposed ways to address both the assessment and treatment of PA regulation from a transdiagnostic perspective [28, 107], but further research is needed on this topic. This study aims to explore the effect of treatment components on increasing wellbeing and PA. If this is confirmed, it would certainly represent an important shift in the research, understanding, assessment, and treatment of ED. To the best of our knowledge, this is the first study of an RCT testing an online transdiagnostic treatment protocol for ED with a specific therapeutic component to directly up-regulate PA.

The data obtained with this study can be compared to results obtained in studies with face-to-face transdiagnostic protocols using benchmarking strategies [33]. In addition, the data will also be compared to transdiagnostic protocols applied over the Internet, but without components for up-regulating PA [15, 108–112].

The objective of establishing action strategies to improve access to EBTs should also be taken into consideration, as well as the goal of providing psychological support to all those in need [5]. Undoubtedly, we are witnessing the beginning of a new era in the field of psychological treatments. They have already gone beyond traditional EBTs, and now it is possible to manage these online protocols with good results [53]. The use of technology and the Internet can help to disseminate and increase the access to these interventions.

Finally, we will test the effectiveness of the application of this Internet-based program with minimal support from the clinician, and the acceptability of this online program in patients from a community sample.

We are aware that this study has limitations. One of the most important is the different number of modules in the two protocols. We tried to control this by giving all the participants equal time and allowing them to use the program as much as they like throughout the whole process. However, in order to test the potential additional impact of the positive psychology component, it seemed necessary to compare it to the traditional transdiagnostic protocol. If the new component is found to have any effect, future research should be carried out to show that this effect is not simply due to the larger number of modules in the protocol.

There are further limitations. For example, dropout rates are expected to be high (around 30%) [53, 63]. To minimize this problem, human and ICT support will be provided. In addition, another limitation may be recruitment difficulties, to the extent that people still do not have access to the Internet at home, or they have negative attitudes towards Internet interventions.

In summary, this study aims to contribute to the literature on the efficacy of transdiagnostic approaches to ED in general, and it more specifically seeks to explore the possible impact of specific component designed to up-regulate positive affect. Despite its limitations, if positive results are achieved, they will have a clear impact on the design and application of future transdiagnostic treatment protocols for ED, as a way to more effectively address the temperament vulnerabilities, that is, the core aspects of these disorders [102].

## Abbreviations

ADNOS: Anxiety Disorder Not Otherwise Specified
AES: Advanced Encryption Standard
AG: Agoraphobia
ANOVA: Analysis of variance
BAI: Beck Anxiety Inventory
BDI-II: Beck Depression Inventory-II
BL: Baseline
CBT: Cognitive Behavior Therapy
CONSORT: Consolidated Standards Of Reporting Trials
DD: Dysthymia
DSM-IV: Diagnostic and Statistical Manual of mental disorders, fourth text
E/PA/BA: Extraversion/Positive Affect/Behavioral Activation
EBTs: Evidence-based psychological treatments
ED: Emotional disorders
EDBs: Emotion Driven Behaviors
EQ-5D: EuroQol-5D questionnaire
FU: Follow-Ups
GAD: Generalized Anxiety Disorder
ICD-10: International Classification of Diseases, tenth edition
ICT: Information and Communication Technologies
MDD: Major Depression Disorder
MDNOS: Mood Disorder Not Otherwise Specified
MINI: Mini-International Neuropsychiatric Interview
N/NA/BI: Neuroticism/Negative Affect/Behavioral Inhibition
NEO-FFI: NEO Five Factor Inventory
OASIS: Overall Anxiety and Impairment Scale
OCD: Obsessive-compulsive Disorder
OCI-R: Obsessive-Compulsive Inventory-Revised
ODSIS: Overall Depression and Impairment Scale
PANAS: Positive and Negative Affect Schedule
PD: Panic Disorder
PDSS-SR: Self-Reported Panic Disorder Severity Scale
POST-T: Post-Treatment
PSWQ: Pen State Worry Questionnaire
RCT: Randomized Controlled Trial
SAD: Social Anxiety Disorder
SI: Social Index
SIAS: Social Interaction Anxiety Inventory
TIBP: Transdiagnostic Internet-Based Protocol
TIBP + PA: Transdiagnostic Internet-Based Protocol + Positive Affect Component
UP: Unified Protocol
VAS: Visual Analogical Scale
WBT: Well-Being Therapy
WL: Waiting List
